Therefore, the placebo-controlled, assessor-blinded randomized trial will be design in the present protocol, which will include group A (IAI-placebo), group B (IAI-PRP), group C (TC + IAI-placebo), and group D (TC + IAI-PRP). This protocol will allow to be achieve the study purpose as follows:

Aim 1: To examine the effectiveness and safety of combined IAI-PRP and TC for KOA treatment by comparing the group D vs B or C.

Aim 2: To compare the differences of efficacy between the IAI-PRP and TC in the KOA treatment by comparing the group B and C.

Aim 3: To provide high-quality evidence of PRP for KOA treatment by comparing the group B and A.

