## Methods/Design

### Study design

This protocol will be a placebo-controlled, assessor-blinded randomized trial, which will be included 12-week intervention and 1-year follow-up. This protocol will be conducted in accordance with the Standard Protocol Items: Recommendations for Interventional Trials (SPIRIT) [25]. A total of 212 patients diagnosed with KOA will be randomly and equally assigned into the group A (IAI-placebo), group B (IAI-PRP), group C (TC + IAI-placebo), and group D (TC + IAI-PRP). A brief flowchart of the entire study is shown in Fig. 1, and the schedule of events is provided in Table 1. The study protocol was approved by the Ethics Committee of Shanghai Seventh People’s Hospital (2022-7th-HIRB-067) and registered in the Chinese Clinical Trial Registry (ChiCTR2300067559).

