### Sample size

The sample size will be determined based on the priori power analysis through G*Power software version 3.1.9.2 [26]. In the calculations, ANOVA repeated measures between factor will be chosen, effect size 0.25, alpha 0.05, power 0.80, number of groups 4, number of measures 5, and the sample size is calculated as 168. Taking into account a conservative anticipation of a 20% drop-out rate, the final sample size will therefore be 53 in each group, with a total of 212 subjects.

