### Statistical analysis

All statistical analyses will be performed with IBM SPSS (Version 22.0, Chicago, IL, USA) by statisticians who are blinded to the group allocation. The outcomes analyses will be performed on an intention-to-treat basis. For the missing data, several sensitivity analyses will be conducted to evaluate their effects on the results. The Shapiro–Wilk will be used to test the normal distribution of the continuous variables for demographic and outcome measures. Continuous variables will be described as mean ± SD for normal distributions or median for non-normal distributions, categorical variables will be described as frequency. The χ^2^ test or Fisher’s exact test will be used to examine the comparisons between the four groups for categorical variables. When the normality of data distribution is found, two-way of variance with repeated measures will be applied to examine the main effects of the group and the time factor and group-time interaction effects. A simple effect post hoc analysis will be conducted, when time-group interaction is significant. Additionally, if homogeneity is not found, a linear mixed model will be adjusted for gender and KL grade. To mitigate bias and potential confounding variables, the propensity score matching (PSM) method will be employed [50]. Significant level for all tests will be set at 0.05 for all statistical tests and corrected for multiple comparisons using the Bonferroni-adjusted method, and 95% confidence interval will be reported.

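### Single-step Bonferroni for the pairwise group contrasts is valid, but Holm's step-down version gives the same error control with somewhat more power: about 2 points at the protocol's own effect size

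*Protocol article*

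**What the plan says.** The Statistical analysis section fixes the significance level ("Significant level for all tests will be set at 0.05 for all statistical tests") and the correction: "corrected for multiple comparisons using the Bonferroni-adjusted method, and 95% confidence interval will be reported". It does not list the family of comparisons.

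The aims at the end of the Background name four pairwise contrasts: D vs B and D vs C (Aim 1, "by comparing the group D vs B or C"), B vs C (Aim 2) and B vs A (Aim 3).

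The Sample size section plans on an overall test of the four groups, not on these contrasts: "ANOVA repeated measures between factor will be chosen", with "effect size 0.25, alpha 0.05, power 0.80, number of groups 4, number of measures 5, and the sample size is calculated as 168". An allowance for 20% drop-out then raises the total to 212, or 53 per arm.

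**The concern.** Every aim is a pairwise comparison and will be judged after correction, whereas the sample size rests on an omnibus test at 0.05 with no allowance for multiplicity. Pairwise power is therefore scarce. Single-step Bonferroni holds every contrast to 0.05/k, whatever the other contrasts show. Holm starts at the same cut-off but relaxes it after each rejection, so its gain comes when several contrasts are truly non-null. The question is how much power the single-step version gives up, in particular for showing that the combination beats each single treatment.

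**Working it through.** **Inputs from the protocol article.** Four equal arms; f = 0.25, alpha 0.05, power 0.80, five measures, 168 evaluable, 20% drop-out (Sample size); four named contrasts (Background); Bonferroni at 0.05 (Statistical analysis).

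**Assumed, because not stated.** Two-sided tests; a family of two (Aim 1 only), four (all aims) or six (all pairs); the pattern of group means.

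**1. The plan's own figures.** For the between-group F test, λ = f²·N·m / (1 + (m−1)ρ), with 3 and N−4 degrees of freedom and m = 5. The correlation ρ is not given. The required N is 112 at ρ = 0.5, 152 at 0.8, 168 at 0.90 to 0.92 and 180 at 1.0. So 168 is reachable with ρ near 0.9; it is neither confirmed nor shown wrong. The drop-out step reproduces: 168/0.8 = 210, or 52.5 per arm, rounded up to 53, and 4 × 53 = 212. Evaluable patients per arm: 168/4 = 42.

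**2. Cut-offs.** With 4 × 41 = 164 error degrees of freedom, the two-sided t cut-off is 1.97 uncorrected, 2.53 at 0.05/4 and 2.67 at 0.05/6. Bonferroni applies the corrected value to every contrast. Holm compares the ordered p-values with 0.05/k, 0.05/(k−1), … 0.05 and stops at the first failure.

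**3. From f to a pairwise effect.** If PRP and Tai Chi are each worth d SD and add up, the means are (0, d, d, 2d). Their deviations from the grand mean are (−d, 0, 0, d), so f = √(2d²/4) = d/√2. Hence f = 0.25 gives d = 0.354, while d = 0.5 gives f = 0.35 and d = 0.6 gives f = 0.42.

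**4. Simulated power for D to beat both B and C** (42 per arm, one score per patient, pooled SD):

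| d per treatment | f | Family | Bonferroni | Holm | Gain (points) |
|---|---|---|---|---|---|
| 0.354 | 0.25 | 4 | 8.0% | 10.1% | 2.1 |
| 0.354 | 0.25 | 6 | 5.9% | 8.3% | 2.4 |
| 0.5 | 0.35 | 4 | 25.2% | 31.1% | 5.9 |
| 0.5 | 0.35 | 6 | 20.3% | 28.3% | 8.0 |
| 0.6 | 0.42 | 4 | 42.7% | 51.4% | 8.7 |
| 0.6 | 0.42 | 6 | 36.8% | 49.2% | 12.4 |

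With no true effect, the familywise error is about 4% for both methods. In no simulated trial did Bonferroni reject a contrast that Holm did not.

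**5. Other success rules and patterns at f = 0.25.**
- D vs B alone, additive pattern, 42 per arm: 18.8% to 20.0% (four contrasts), 15.2% to 17.8% (six).
- At least one of D vs B and D vs C, same setting: 29.4% to 30.1% (four).
- The ranges below cover five mean patterns with D above B and C, 42 or 53 per arm, and a variance of 1 or 0.6. The latter is the mean of five visits at ρ = 0.5: (1 + 4 × 0.5)/5.
  - Both contrasts: gain 1.3 to 6.3 points (four), 1.5 to 8.3 (six).
  - At least one: 0 to 2.9 (four), 0.4 to 5.9 (six).
- If Aim 1's two contrasts formed a family of their own: 4.2 to 11.0 points for both, and exactly 0 for at least one, because Holm's first step is the Bonferroni step.

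**Limit.** The plan runs its post hoc comparisons only after a significant group-time interaction. That gate is not modelled, so the absolute powers are indicative and the differences between methods are what matter.

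**The case against.** The strongest objection is that there is no defect: Bonferroni is valid, prespecified and conservative, and nothing in the article conflicts with it. That stands, and it sets the level of this point as an optional improvement. It does not remove the point, because the article itself fixes the method and a uniformly at least as powerful one is available for the same tests.

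A reader might infer that Aim 1 forfeits some 6 to 12 points of power. The documents do not support that as a figure for this trial. For the four- and six-contrast families it was obtained with effects of 0.5 to 0.6 SD (f of 0.35 to 0.42), larger than the planned 0.25, and it requires D to beat both B and C. The aim is worded "by comparing the group D vs B or C" and does not say that both must succeed.

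A reader might also infer that the power is given up for nothing. That is too strong. Bonferroni tests come with simple simultaneous intervals that agree with them, and the same sentence of the plan promises confidence intervals. Holm has no equally simple match, which is a real if small cost.

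Finally, Holm would not rescue Aim 1: at f = 0.25 with additive effects, the power to beat both comparators is only about 8% to 10% with either method (four contrasts, 42 per arm).

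**Conclusion.** The point holds as a cheap improvement of low severity. The direction of the gain is certain: whichever family is used, Holm keeps the 5% familywise error and rejects everything Bonferroni rejects. Its size depends on what the article leaves open. For beating both comparators it is about 2 points in the additive case at the planned f = 0.25 with 42 per arm, and about 1 to 8 points over the other patterns examined with four or six contrasts. If one win is enough, it is generally smaller, and nil when Aim 1's two contrasts are the whole family. The weakness of an omnibus sample-size basis remains under either method.

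**What to change.** In the Statistical analysis section, replace the Bonferroni adjustment by the Holm step-down method for the pairwise group contrasts: order the unadjusted p-values and compare them with 0.05/k, 0.05/(k−1), … 0.05, stopping at the first that fails. State k.

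Report Bonferroni-level simultaneous intervals beside the unadjusted 95% intervals, each labelled: 1 − 0.05/4 = 98.75% for four contrasts, or 1 − 0.05/6 = 99.17% for six. The label matters because an unadjusted 95% interval (cut-off 1.97) can exclude zero when the corrected test fails (2.53 for four contrasts).

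The cost is one change of wording and a sort of the p-values, with no extra patients and no higher false-positive limit, provided the change is made before unblinding. The downside should be stated in the plan. As an illustration with four contrasts, ordered p-values of 0.010 and 0.015 both pass Holm (0.0125, then 0.05/3 = 0.0167), yet the 98.75% interval for the second includes zero because 0.015 exceeds 0.0125.

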### Patient and public involvement

The initial study idea was conceived by the study team. The patients with KOA, physiotherapists and neurologist took part in preparation of the proposal with face-to-face interviews. In addition, the study protocols also will be modified and supplemented utter concerns not addressed in a draft proposed at the time based on their feedback, to ensure the safety and applicability of the intervention.

### Dissemination plans

The results of this study will be fully published in international peer-reviewed journals, with both positive and negative results reported.

## Discussion

The systematic review reported that no treatment methods have significant modifying properties and long-term efficacy for KOA [2, 11]. The development of an ideal and effective programs for treatment of KOA is still being explored. The pathological mechanisms of KOA involved the progress of the biochemical and biomechanical [8, 51], but no integrated treatment programs for the aspects of the biomedical and biomechanical mechanisms. In our knowledge, this trial is first one to propose an integrated scheme combing IAI-PRP and TC for treatment of KOA, based on the consideration of the biochemical and biomechanical pathogenesis of KOA. Furthermore, the efficacy, acceptability and safety of the combined IAI-PRP and TC will be explored by the design of 12-week intervention and 12-month follow-up. These results of the study will provide evidence with high quality for integrated IAI-PRP and TC, and guide significance for design more effective treatment methods in KOA.

This study has several important strengths. First, it is a novel integrated treatment method for combing PRP IAI and TC interventions for KOA. Previous study examined individual components (e.g., health education, PRP, TC) but have not combined them in an integrated method [16, 22, 52]. More importantly, this method takes into account the biochemical and biomechanical factors in the development of KOA, and may have a potential opportunity to treat KOA. Second, the comprehensively intervention protocol will be evidence-based and rigorously developed based on the evidence, recommendations, theories and practice standards of the systematic review [30, 40, 53], and will be allowed to achieve multiple study purpose such as examine the effectiveness and safety of combined IAI-PRP and TC for KOA treatment and compare the differences of efficacy between the IAI-PRP and TC in the KOA treatment. The questions will be answered by these study purposes which are also the problems that the need to be solved in the field of KOA treatment in the systematic review wrote by Cook [6]. Third, Medical Research Council Framework for developing and evaluating complex interventions suggested that the feasibility, acceptability and safety of a proposed intervention and research methodological procedures should be fully examined prior to performing the full-scale study [54, 55]. The comprehensive assessment of efficacy, acceptability and safety was designed in this study, such as drop-out rate will be reflected acceptability and adverse events occur rate will be reflected safety. Last, more systematic and comprehensive assessment outcomes will be selected in this protocol, such as knee adduction moment from 3D gait analysis, inflammatory factor levels from venous blood and synovial fluid. Therefore, the present study will provide more comprehensive and systematic protocol for the further study with randomized controlled.

We recognize this study also has limitations. This research has an inevitable limitation associated with the difficulty in controlling the methodology of blinding during the TC intervention, which cannot be blinded for the participants and therapists due to the visible of the TC intervention. Although the outcome assessors and data analyzer will be blinded to the group allocation, which might increase the risk of detection bias during the study’s implementation. Additionally, the PRP preparation and injection need to be operated by medical personnel in medical institutions, which may limit the promotion and application of the combined IAI-PRP and TC in the community and home.

In summary, the results of the study protocol will demonstrate that the efficacy, acceptability and safety of the combined IAI-PRP and TC for treatment of KOA. This method may have a potential opportunity to treat KOA. The study protocol will provide guide significance in integrate exist and different rehabilitation technology and design more effective rehabilitation program for KOA.

## Data Availability

Not applicable.

## Abbreviations

KOA: Knee osteoarthritis
IAI: Intra-articular injection
PRP: Platelet-rich plasma
HA: Hyaluronic acid
MSCs: Mesenchymal stem cells
TC: Tai Chi
MRI: Magnetic resonance image
CT: Computed tomography
KL: Kellgren–Lawrence
OARSI: Osteoarthritis Research Society International
ESCEO: Osteoarthritis and Musculoskeletal Diseases
CBCs: Complete blood counts
WOMAC: Western Ontario and McMaster Universities Osteoarthritis Index
CRF: Case report form
TUG: Timed up and go test
IL-1 β: Interleukin-1 β
IL-6: Interleukin-6
VEGF: Vascular endothelial growth factor
ELISA: Enzyme-linked immunosorbent assay
TNF-α: Tumor necrosis factor α
SF-36: 36-Item short form health survey
